### Study objectives

This study aims to systematically characterize the 5-year natural history of pDoC through a prospective cohort design, thereby bridging the critical evidence gap stemming from the absence of large-scale, long-term follow-up investigations. The specific objectives are as follows:To determine the rates of consciousness recovery, all-cause mortality, and major cardiovascular events over a 5-year follow-up period in patients stratified by initial level of consciousness (VS, MCS−, and MCS+); primary comparisons will be conducted at the VS vs. MCS level, with MCS − vs. MCS + differentiation examined in prespecified subgroup analyses.To identify etiology, injury severity (GCS at admission), time from injury to enrollment, Coma Recovery Scale–Revised (CRS-R) subscale profiles, and neuroimaging indices as independent predictors of consciousness recovery and unfavorable outcomes.To develop and validate a multimodal prognostic prediction model integrating clinical, neuroimaging, and biomarker data.

The primary research question of this study is: among patients with prolonged disorders of consciousness (VS or MCS ≥ 28 days post-acute brain injury), does baseline consciousness level (VS vs. MCS) independently predict 5-year consciousness recovery trajectory, after adjustment for etiology, injury severity, and neuroimaging characteristics?

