#### Exposure variable

The primary exposure variable is the baseline level of consciousness (VS or MCS) at enrollment. All enrolled participants will receive standardized multimodal rehabilitation care in accordance with the Chinese Expert Consensus on the Diagnosis and Treatment of Prolonged Disorders of Consciousness (Standard of Care, SOC) (10), encompassing: (1) pharmacological arousal-promoting therapy (e.g., amantadine, donepezil, zolpidem); (2) multimodal sensory stimulation therapy (auditory, tactile, visual, and olfactory modalities); (3) physical therapy (including tilt-table training and passive mobilization); (4) occupational therapy; (5) speech-language therapy; (6) hyperbaric oxygen therapy (where indicated and available); and (7) neuromodulation techniques (e.g., median nerve electrical stimulation, repetitive transcranial magnetic stimulation, spinal cord stimulation), as well as evidence-based complication management (infections, spasticity, pressure injury). Treatment intensity for each modality will be quantified as total weekly contact time (minutes per week) and session frequency, recorded prospectively in the electronic data capture system at each assessment timepoint. All treatment variables will be incorporated as time-dependent covariates (operationalized as weekly contact time (min/week) per rehabilitation modality) in the analytical models to distinguish the natural disease course from treatment-mediated effects.

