#### Predictor variables and covariates

Primary prognostic predictor variables have been selected based on established clinical and biological plausibility for predicting consciousness recovery: (1) etiology of brain injury (TBI, hypoxic-ischaemic encephalopathy, cerebrovascular event, metabolic/toxic encephalopathy, other), given that neurobiological recovery trajectories differ substantially across aetiological subgroups; (2) injury severity at the acute phase (GCS score at hospital admission); (3) time from acute brain injury to study enrollment; (4) CRS-R subscale scores at baseline (auditory, visual, motor, oromotor/verbal, communication, and arousal subscales); and (5) neuroimaging characteristics (white matter integrity on DTI, functional connectivity on fMRI). Pre-injury lifestyle characteristics [smoking status, alcohol consumption, physical activity (assessed via caregiver proxy report using IPAQ) (11), and dietary habits] are retained as exploratory secondary covariates; their collection is hypothesis-generating and their role as determinants of post-injury recovery will be interpreted with appropriate caution given the reliance on caregiver proxy report.

Pre-specified adjustment covariates in all multivariable models include age, sex, educational level, and comorbidities (e.g., cardiovascular disease, diabetes mellitus, chronic kidney disease). It should be noted that injury severity (GCS at acute admission) and the interval from injury to enrollment are designated as primary prognostic predictor variables in this study (see above), rather than as confounders, given their established direct effects on consciousness recovery trajectories; they will therefore enter the analytical models as predictors of interest rather than as adjustment terms. Effect modifiers—including age stratum (< 50 years vs. ≥50 years), injury type (traumatic vs. non-traumatic), and baseline CRS-R score—will be formally evaluated through prespecified subgroup analyses and interaction testing.

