### Sample size calculation

The sample size was determined based on 5-year consciousness recovery rates reported in the existing literature on prolonged disorders of consciousness. Chen et al. (13) reported a 5-year consciousness recovery rate of 42.3% in a prospective cohort of Chinese patients; a systematic review by Giacino et al. (14) indicated recovery rates of approximately 35–50% among patients with pDoC following TBI; and a recent longitudinal study by Yan et al. (15) reported a 5-year cumulative recovery rate of 48.7%. Given that the present study enrolls a mixed-etiology cohort (traumatic and non-traumatic) and employs a competing-risk analytical framework, a conservative 5-year cumulative incidence rate of 34% (annual event rate: 8%) was adopted as the basis for sample size estimation, ensuring adequate statistical power. Assuming a hazard ratio (HR) of 1.3, two-sided *α* = 0.05, 80% statistical power, and an exposure proportion of 30%, the required number of events was calculated as 544 using the Schoenfeld formula. Adjusting for an anticipated 15% loss to follow-up over the 5-year period, the target sample size was determined to be 1,000 participants. This sample size will ensure adequate statistical power for the primary survival outcome, support detection of secondary outcomes (functional recovery and quality-of-life changes), enable the identification of moderate effect sizes (Cohen’s *d* ≥ 0.5 or OR ≥ 1.5), and accommodate prespecified subgroup analyses. Prespecified subgroup analyses will evaluate the influence of age, sex, and baseline severity; assuming a subgroup prevalence of 30% and an event rate consistent with the overall cohort, ≥ 80% power will be achievable for detecting HR ≥ 1.5 within each subgroup.

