### Subgroup and interaction analyses

Prespecified subgroup analyses will be conducted based on clinical relevance and potential effect modification, including: age (< 50 years vs. ≥ 50 years), sex (male vs. female), injury type (traumatic vs. non-traumatic), and baseline level of consciousness (VS vs. MCS). Interaction terms (product terms between the exposure variable and subgroup variables) will be introduced into multivariable regression models to formally test the statistical significance of interactions, with a significance threshold of *p* < 0.10. Statistically significant interactions will be further examined through stratified subgroup analyses, with results displayed as forest plots showing HRs and 95% CIs for each subgroup. All subgroup analyses will be characterized as exploratory findings to prevent overinterpretation.

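### Objective 1 sends MCS− vs MCS+ to the subgroup analyses, but the subgroup section lists only VS vs MCS, and its product-term method cannot deliver the contrast

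*Protocol article*

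**What the plan says.** Study objectives: the first objective concerns 5-year rates of recovery, death and major cardiovascular events (MACE), with patients stratified as VS, MCS− and MCS+. It ranks the comparisons: "primary comparisons will be conducted at the VS vs. MCS level", with the MCS−/MCS+ "differentiation examined in prespecified subgroup analyses".

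Exposure variable: "The primary exposure variable is the baseline level of consciousness (VS or MCS) at enrollment".

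Subgroup and interaction analyses: the listed subgroups are age, sex, injury type "and baseline level of consciousness (VS vs. MCS". The method follows: "Interaction terms (product terms between the exposure variable and subgroup variables) will be introduced into multivariable regression models", tested at p < 0.10, and then "Statistically significant interactions will be further examined through stratified subgroup analyses". All subgroup analyses are labelled exploratory.

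Two other places list subgroups or effect modifiers. Predictor variables and covariates names age stratum, "injury type (traumatic vs. non-traumatic), and baseline CRS-R score". Sample size calculation says: "Prespecified subgroup analyses will evaluate the influence of age, sex, and baseline severity". Neither names MCS−/MCS+.

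Primary analysis plans cumulative incidence functions and Fine-Gray models for recovery and Cox models for death. It mentions no MCS−/MCS+ term, and neither does Sensitivity analyses.

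**The concern.** The objectives send a named comparison to a named place, and that place holds a different comparison. The consciousness entry in the subgroup list repeats the exposure instead of splitting MCS.

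Adding MCS−/MCS+ to the list would not be enough. The split is a finer level of the exposure, defined only inside one of its two categories. It is not a characteristic that VS and MCS patients share and that could modify a VS vs MCS effect, so an exposure-by-subgroup product is the wrong tool for it.

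At stake is one component of the first objective. Without a workable specification, the coding, adjustment set and reporting of the MCS+ vs MCS− comparison would be settled during analysis. The primary question, VS vs MCS, is not affected.

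**Working it through.** **1. The lists side by side**

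| Section | Consciousness or severity entry | MCS−/MCS+ named? |
|---|---|---|
| Study objectives | VS, MCS−, MCS+; the MCS split sent to subgroup analyses | Yes |
| Exposure variable | VS or MCS | No |
| Predictor variables and covariates (effect modifiers) | Baseline CRS-R score | No |
| Sample size calculation (subgroups) | Baseline severity, not defined further | No |
| Subgroup and interaction analyses | VS vs MCS | No |

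**2. What the stated method gives.** Let E = 0 for VS and 1 for MCS. Let M = 1 for MCS+ and 0 otherwise. Only three cells exist: VS (E=0, M=0), MCS− (1, 0) and MCS+ (1, 1).

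- *Subgroups age, sex and injury type, each with its product with E.* The exposure, subgroup and product columns are identical for an MCS− and an MCS+ patient of the same age stratum, sex and injury type. No coefficient separates the two.
- *Listed subgroup VS vs MCS.* The subgroup variable is E, and E × E = E. Intercept, E, E and E × E have rank 2 for 4 columns, so there is no interaction to test.
- *MCS−/MCS+ added under the same method.* No VS patient can be MCS+, so E × M = M in every cell. Intercept, E, M and E × M have rank 3 for 4 columns. The interaction is not estimable, and no p-value can lead on to stratified analysis.
- *Stratifying without the interaction test.* Within VS, MCS, MCS− or MCS+ the exposure is constant, so no exposure hazard ratio exists in any stratum.

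**3. What works.** Intercept, E and M (equivalent to a three-level factor) have rank 3 for 3 columns. The coefficient of M is the MCS+ vs MCS− log hazard ratio.

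**4. Precision of the repaired contrast.** The claim does not depend on this step. The Schoenfeld formula is events = (z₀.₉₇₅ + z₀.₈₀)² / [p(1 − p)(ln HR)²].

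Check against the protocol's own figure, with HR 1.3 and p = 0.30: 2.8016² / (0.21 × 0.2624²) = 542.97, so 543 against the stated 544. The formula is reproduced.

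The protocol gives neither the MCS share nor the MCS+ share. Its exposure proportion of 30% does not say which level is meant. Assumptions: MCS is 30–70% of 1,000, MCS+ is 30–50% of MCS, 34% have the event (the protocol's 5-year rate), and 15% are lost (its anticipated loss), with those lost contributing no events.

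- Lowest: 1,000 × 0.30 × 0.34 × 0.85 = 86.7 events. With p = 0.30, detectable HR = exp[2.8016 / √(86.7 × 0.21)] = exp(0.657) = 1.93.
- Highest: 1,000 × 0.70 × 0.34 × 0.85 = 202.3 events. With p = 0.50, detectable HR = exp[2.8016 / √(202.3 × 0.25)] = exp(0.394) = 1.48.

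Across these ranges, power is 20–46% for HR 1.3 and 41–82% for HR 1.5.

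**The case against.** The strongest reply is that this is a small mismatch in a condensed article. The subgroup list is introduced as non-exhaustive, its opening sentence does not make subgroup analyses conditional on an interaction test, and model detail may sit in an analysis plan that is not shown. The rank argument for MCS−/MCS+ also applies the stated method to a subgroup that the section never lists.

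Part of this stands. Three stronger readings might be inferred, and the document does not support them.

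- *Part of objective 1 gets no analysis at all.* The objective is framed in rates, and cumulative incidence functions are planned. Drawn by the three strata that the objective names, they would describe recovery without any interaction model. What is missing is a regression contrast.
- *Any later MCS+ vs MCS− estimate would be post hoc.* The objectives name the contrast, the outcomes, the horizon and its rank below VS vs MCS. It is prespecified in intent.
- *The contrast has good power.* With 70% MCS, an even split and no loss there would be 238 events and a detectable HR of about 1.44. That is a single best case, and it ignores the protocol's own 15% loss.

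The rest of the reply does not remove the point. The article states both the promise and the list and method meant to keep it, and they disagree. The degeneracy is not only hypothetical: the VS vs MCS entry that is listed is the exposure crossed with itself. An open list does not help when the one stated method cannot produce the contrast. Dropping the redundant product term would leave an estimable MCS+ coefficient, but that is a main effect within MCS and not the interaction test described.

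**Conclusion.** The point holds as an internal contradiction with an unworkable rule. Study objectives and the subgroup section disagree on which consciousness contrast is a subgroup analysis. The stated method is degenerate for the contrast that is listed and would be degenerate for the one that was promised. No regression analysis in the article delivers MCS+ vs MCS−. This conclusion follows from the definitions and needs no assumed figure.

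The consequence is limited. The contrast is subordinate and exploratory, rates by stratum remain obtainable, and the primary comparison stands. Under the assumed shares, with about 87–202 events and a detectable HR of about 1.5 to 1.9, the repaired contrast is mainly an estimate with an interval. The correction is cheap and should be made.

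**What to change.** In Subgroup and interaction analyses:

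- Remove VS vs MCS as a subgroup of itself. Replace it with a direct MCS+ vs MCS− contrast, from a model with exposure as a three-level factor (VS, MCS−, MCS+) or from a model within MCS patients.
- Apply it to all three outcomes in the objective: Fine-Gray for recovery, Cox for death, and a named model for MACE.
- Keep it outside the p < 0.10 interaction test.
- State which of Models 1–5 carries it. Models 4 and 5 adjust for baseline CRS-R total, and level of consciousness is itself assessed with the CRS-R, so this choice decides what the contrast means.
- Report cumulative incidence by the three levels. Keep VS vs MCS primary and the new contrast exploratory, given as an estimate with its confidence interval.

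Align the lists in Predictor variables and covariates and in Sample size calculation with the corrected one.

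The cost is protocol wording and one extra model per outcome. No new data are needed, because MCS− and MCS+ are already distinguished in the study population and in the objective's strata. Enrolment is planned from June 2026, and the wording should be settled before outcomes accrue.

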## Statistical analysis methods

### General principles and descriptive statistics

All statistical analyses will employ two-sided tests with a significance threshold of α = 0.05, and results will be reported with 95% confidence intervals. Bonferroni correction or false discovery rate (FDR) adjustment will be applied to control Type I error inflation in the context of multiple comparisons. Multivariable regression models will be constructed within the competing-risk framework to identify independent prognostic predictors of consciousness recovery, as detailed in the Primary Analysis subsection below. Separately, a dedicated multimodal prognostic prediction model will be developed and validated using a three-stage hierarchically nested approach incorporating LASSO-based variable selection and bootstrap internal validation (1,000 resampling iterations); the C-index will serve as the primary discrimination metric. The full construction procedure for this prediction model is described in the dedicated subsection below.

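### Stratified subgroup hazard ratios and forest plots are tied to interactions reaching p < 0.10, and the prespecified subgroup factors differ between sections, so the displayed effects risk being selected and exaggerated

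*Protocol article*

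**What the plan says.** The section Subgroup and interaction analyses opens without a condition: "Prespecified subgroup analyses will be conducted based on clinical relevance and potential effect modification". It names age, sex, injury type, and VS versus MCS. Product terms between the exposure and these factors are tested "with a significance threshold of *p* < 0.10". The next step is: "Statistically significant interactions will be further examined through stratified subgroup analyses, with results displayed as forest plots". It closes with: "All subgroup analyses will be characterized as exploratory findings to prevent overinterpretation".

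The section General principles and descriptive statistics sets a general rule, "All statistical analyses will employ two-sided tests with a significance threshold of" 0.05, and adds: "Bonferroni correction or false discovery rate (FDR) adjustment will be applied to control Type I error inflation in the context of multiple comparisons". It defines no family and does not mention interaction tests.

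Three other sections also describe the subgroup factors:
- Study objectives puts MCS− versus MCS+ into prespecified subgroup analyses.
- Predictor variables and covariates lists age stratum, "injury type (traumatic vs. non-traumatic), and baseline CRS-R score" as effect modifiers for prespecified subgroup analysis and interaction testing.
- Sample size calculation says: "Prespecified subgroup analyses will evaluate the influence of age, sex, and baseline severity".

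The section Exposure variable defines the primary exposure as baseline consciousness level, VS or MCS.

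**The concern.** Two features combine. First, the only display of subgroup-specific HRs that the protocol describes is attached to interactions that passed a significance test. (The forest plots under Primary analysis show estimates across adjustment models, not across subgroups.) An estimate shown because it crossed a threshold is on average further from the null than the truth. If the subgroups that did not pass are not shown beside it, a reader cannot see what it was selected from.

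Second, the set of factors called prespecified is not fixed. With several lists in force, which factors count as planned could be settled after the data are seen, which defeats the purpose of prespecification. The multiplicity position of the tests is also open, so the false-positive risk of the screening step cannot be read off the plan.

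**Working it through.** **1. The lists side by side**

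| Section | Age | Sex | Injury type | Baseline severity or consciousness level |
|---|---|---|---|---|
| Study objectives | – | – | – | MCS− vs MCS+ |
| Predictor variables and covariates | yes | – | yes | CRS-R score |
| Sample size calculation | yes | yes | – | severity, not defined |
| Subgroup and interaction analyses | yes | yes | yes | VS vs MCS |

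No factor appears in all four. Age is the only one that is common to the last three. VS versus MCS is the exposure, so a product term of the exposure with itself adds no information and cannot be estimated. That leaves three testable factors in the fourth list: age, sex and injury type.

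**2. False interactions, if 0.10 is applied without correction**

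For k independent tests with no true interaction, the chance of at least one p < 0.10 is 1 − 0.9^k. For k = 3 on one outcome: 1 − 0.9³ = 0.271, or 27%.

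**3. The plan's own event figure**

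Schoenfeld with HR 1.3, two-sided 0.05, 80% power and 30% exposed: (1.960 + 0.842)² / (0.3 × 0.7 × (ln 1.3)²) ≈ 543, against 544 stated. The figure is reproduced to within one event, so the same variance formula is used below.

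**4. What passes the threshold, and how large it looks**

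Inputs from Sample size calculation: 34% five-year incidence in 1,000 patients gives 340 events; the required figure of 544 is used as a second case; 30% are exposed. Assumptions made here: subgroup splits of 50/50 and 30/70, events divided in the same proportions, and a true ratio of HRs of 1.3. (The protocol's 1.3 is a main-effect HR; it is borrowed only as a plausible size.)

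- SE of the log ratio of HRs = √[1/(0.21·E₁) + 1/(0.21·E₂)], where E₁ and E₂ are the events in the two subgroups.
- Smallest ratio that passes = exp(1.645 × SE).
- Mean displayed log ratio ≈ μ + SE·φ(a)/(1 − Φ(a)), with μ = ln 1.3 = 0.262 and a = (1.645·SE − μ)/SE.

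Example, 340 events split 50/50: SE = √(2/(0.21 × 170)) = 0.237. Threshold = exp(0.389) = 1.48. a = 0.54, mean log ratio ≈ 0.54, exp ≈ 1.71.

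| Events | Split | SE | Smallest ratio that passes | Mean displayed if true ratio is 1.3 | Mean displayed if no interaction |
|---|---|---|---|---|---|
| 340 | 50/50 | 0.237 | 1.48 | 1.71 | 1.63 |
| 340 | 30/70 | 0.258 | 1.53 | 1.79 | 1.70 |
| 544 | 50/50 | 0.187 | 1.36 | 1.56 | 1.47 |
| 544 | 30/70 | 0.204 | 1.40 | 1.61 | 1.52 |

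Ratios below 1 are treated by their inverse, and means are taken on the log scale. The last two columns come from simulation with one million draws per row, which agrees with the formula. At 340 events, an interaction with true ratio 1.3 would pass in about 27% to 30% of studies.

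**The case against.** The strongest reply is that the text is milder than it may appear. Four points deserve weight.

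- A reader might infer that subgroups are shown only when significant. The word only is not there. The section says without condition that subgroup analyses will be done, and the step for significant interactions can be read as an addition. This stands. What remains is that nothing commits the sponsor to displaying the others.
- A reader might infer that the interaction tests are uncorrected. The general Bonferroni or FDR promise does not exempt them, so this is not established, and the 27% holds only if no correction is applied. A correction would lower that figure. It would also raise the ratio needed to pass, so it would not cure selection in the display.
- A reader might infer that 0.10 contradicts the general 0.05. A specific, openly stated threshold for low-powered interaction tests can fairly be read as an exception. The open question is its relation to the correction, not the choice of 0.10.
- The lists may be loosely worded more than opposed. Two are introduced as non-exhaustive, and baseline severity, CRS-R score and VS/MCS may overlap. But sex is missing from one list, injury type from another, and MCS− versus MCS+ appears only in Study objectives. A list described as prespecified should not need that reading.

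The exploratory label is also a real safeguard against overclaiming, and no primary conclusion depends on these tests.

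**Conclusion.** The point holds as a risk in the plan, not as a prediction of what will be published. The stratified HRs and forest plots are tied to p < 0.10, the rest have no promised display, the relation of 0.10 to the multiplicity rule is unstated, the subgroup lists conflict across four sections, and one listed factor cannot be tested because it is the exposure.

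The sizes are illustrations. The 27% assumes three independent tests on one outcome without correction. The inflation from 1.3 to about 1.7 to 1.8 assumes 340 events, 30% exposed, splits from 30/70 to 50/50 and a normal approximation; with 544 events it is about 1.6. The documents do not support saying that non-significant subgroups will be withheld, or that the displayed effects will in fact be exaggerated. This should be corrected, but it does not threaten the primary analysis.

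**What to change.** - Use one subgroup list, with cut-points, in Study objectives, Predictor variables and covariates, Sample size calculation, and Subgroup and interaction analyses. Replace the undefined baseline severity with a named variable or drop it.
- Remove VS/MCS as a subgroup for the VS/MCS exposure effect.
- Plot every listed subgroup, with its interaction estimate (ratio of HRs) and 95% CI, whatever the p-value. Stratified results should not depend on p < 0.10.
- State whether interaction p-values are descriptive or covered by the general correction. If covered, name the method and the family of tests.

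The cost is protocol wording and a longer forest plot. No extra data are needed, no sample size figure changes, and enrolment is planned to open only in June 2026.
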